### Assessments

Table 1 displays the different parameters used at each measurement time. They are detailed below.

#### Questionnaires

##### For patients

All questionnaires are detailed in Additional file 1: Appendix 1.

**General information:** Sociodemographic and medical data such as gender, age, language, professional activity, family members, personal history of cancer and treatment are collected. Some questions are also asked about life habits (physical activity, medication, alcohol and drug use, for example), and important life events.

**Physical and psychological functioning** is assessed through the use of several questionnaires: Visual Analogue Scales (VAS), the Edmonton Symptom Assessment Scale (ESAS) [61], the Hospital Anxiety and Depression Scale (HADS) [69], the Penn State Worry Questionnaire (PSQW) [70], the Fear of Cancer Recurrence Inventory (FCRI) [71], the Mental Adjustment to Cancer Scale (MAC) [72], the White Bear Suppression Inventory (WBSI) [73], the Multidimensional Fatigue Inventory (MFI-20) [74], the Cognitive Emotion Regulation Questionnaire (CERQ) [75], the Impact of Cancer Questionnaire (ICQ) [76], the Insomnia Severity Index (ISI) [77], the Five Facets Mindfulness Questionnaire (FFMQ) [78], the Post-traumatic Growth Inventory (PTGI) [79] and the Rosenberg’s self-esteem scale [80].

**Cognitive functioning** is assessed with the Functional Assessment of Cancer Therapy – Cognitive Function (FACT-Cog v.3) [81] and the Metacognition Questionnaire (MCQ-30) [82].

**Conjugal functioning** is assessed using two questionnaires: the Couples’ Illness Communication Scale (CICS) [83] and the Dyadic Coping Inventory (DCI) [84].

**Relaxation strategies** is investigated using two questionnaires about relaxation strategies used during the first exercise and about relaxation habits. These were created for the study.

Finally, the **questionnaire about the intervention** is focused on expected and perceived benefits from the intervention both for oneself and the partner (open questions).

##### For partners

Partners complete five questionnaires:
*Sociodemographic and medical information*
*Hospital Anxiety and Depression Scale* [69]*Couples’ Illness Communication Scale (CICS)* [83]*Dyadic Coping Inventory (DCI)* [84]Expected and perceived benefits from the intervention, for oneself and for the patient.

#### Tasks

Three tasks are suggested to the participants:*Two relaxation exercises:* Anxiety regulation is measured during two relaxation exercises. Before each exercise, anxiety is triggered by the completion of the MAC (before exercise 1) and the ICQ (before exercise 2) questionnaires. During the first exercise, participants have to use their own strategies to relax by themselves for about 13 mins, and during the second, they are guided by an audio recording for approximately the same time. Heart rate (beats per minute) is measured during the exercises by the Lifecard CF holter monitor as an indicator of anxiety regulation [85]. Heart rate variability has been shown to be correlated with emotion regulation [86] and influenced by emotional distress (depression and anxiety) [87, 88].*An attentional task:* A computerized task is used to assess the attentional bias toward threat. This computerized task, designed by the Université Libre de Bruxelles (ULB, Belgium), aims to evaluate the intensity of the attentional bias toward emotional information. Several pairs of words (each word being positive, negative, or neutral; and related or not related to cancer) are presented to the participants, followed by a point, located at the same place as one of the two words. The participants have to click on the up or down button of the keyboard depending of the location of the point. An increased response time for points following cancer-related words could suggest the presence of an attentional bias towards threat. Response time and accuracy will be measured in order to calculate different attentional bias indexes [18], which will evaluate the severity of the bias before and after the intervention.

#### Ecological momentary assessments

Different ecological momentary assessments will be made between the two evaluation sessions with the experimenter.*Emotional regulation:* At each measurement point, participants have to use an application on a smartphone for 9 days. This application was designed by ULB and aims to evaluate the emotional state of the participant at six different times of the day (intensity and perceived controllability of emotions, and energy level).*Activity and sleep measurements*: At each measurement point, participants wear an actigraph (Garmin Vivoactive® HR), which measures their physical activity (number of steps per day) and their sleep (number of hours of deep and light sleep per night and waking time after initial sleep onset) for 9 days. Wrist actigraphs provide an accurate 24-h sleep assessment and activity patterns in a natural environment [89, 90] and have been used in several studies with cancer patients [90–92].

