#### Measurement points (T1, T2 and T3)

Each of these three measurement points is completed by every participant and is divided into two sessions, separated by a 9-day interval (see Fig. 1). We decided to divide into two sessions in order to minimize the burden encountered by the participants. The first session (about 2 h 30 min) is dedicated to the completion of several questionnaires and the realization of two relaxation exercises (see Table 1). During the whole session, a cardiac holter monitor is placed on participants to measure their heart rate. The second session (about 1 h 15 min) is dedicated to a computerized attentional task and to the completion of some questionnaires and open questions (see Table 1). During the 9-day interval, participants wear an actigraph (Garmin Vivoactive® HR) which measures heart rate, physical activity, and sleep. As participants do not have to do anything else with the actigraph than to recharge it, it is not considered to be complicated. The experimenter also installs an application on their smartphone (RealLife Exp, pack LifeData V5), which asks them about their emotions six times a day. In Belgium, 64% of 45–54-year-old use a smartphone, while 53% of people aged of 55 or more use one [64]. We conclude, therefore that it is likely that most of our participants are able to use a smartphone. However, a smartphone is lent to those who don’t have one and explanations are given if necessary. The experimenter also remains available by phone or email between the sessions to answer any question. Some questionnaires for partners are also given to the participants who have one with instructions to ask their spouse to complete them in order to collect data about partners’ well-being. Consent forms for partners are attached to these questionnaires. At the end of the first measurement point, participants are informed of the result of the randomization and their allocation in either the intervention group or the waiting-list control group.

**Table 1 Tab1:** Patients’ measures used in the study

T0 Screening	T1, T2 and T3 Measurement points	T4 Measurement point
*Questionnaires:*	Session 1	*Questionnaires:*
- ESAS (only 6 items)	*Questionnaires* - General information - VAS (psychological state) - ESAS (complete version) - HADS - PSWQ - FCRI - MAC - WBSI - MFI-20 - CERQ - ICQ - ISI	- MFI-20 - HADS - ESAS (complete version) - FCRI - Long-term benefits of the intervention
	*Tasks*	

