### Statistical analyses

Baseline (T1) demographic, medical, and psychological data will be compared between groups to test for initial groups equivalency using inferential statistics, including analyses of variance (ANOVA) and chi-square tests. Group-by time changes, and pre- and post-assessment comparison of each variable within each group will be assessed using repeated measures MANOVA, on the participant who completed all the needed assessments times. The link between a decrease in distress and attentional bias will be assessed by correlations. Correlations will also be used to assess the links between the data from the patients and their partners, and we will measure the evolution of the partners using repeated measures MANOVA. All tests will be two-tailed, and the alpha will be set at 0.05. Statistical analyses will be performed after T3 and after T4.

All participants will be informed by e-mail about the final results of the study. Scientific publications will also be planned.

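### Completer-only repeated-measures MANOVA, fixed for every variable, is a poor method for the smartphone and actigraph data, which are collected at home and unevenly completed

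*Protocol article*

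**What the plan says.** Under Ecological momentary assessments, the protocol article states that "participants have to use an application on a smartphone for 9 days", with emotional state rated "at six different times of the day". Each rating covers "intensity and perceived controllability of emotions, and energy level". Over the same 9 days an actigraph records steps and sleep. The section on T1, T2 and T3 says: "Each of these three measurement points is completed by every participant and is divided into two sessions"; the app and actigraph period lies between the two sessions. T4 has questionnaires only.

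For change over time by group, Statistical analyses names one method: "comparison of each variable within each group will be assessed using repeated measures MANOVA". The analysis set is given as "on the participant who completed all the needed assessments times". No outcome is exempted. The other methods named there (ANOVA and chi-square at baseline, correlations for associations) do not address change by group.

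The One-year follow-up section calls missing responses very unlikely because an investigator is present and checks each questionnaire. The Discussion, on limitations, concedes that those who finish every assessment may be the motivated and compliant patients, which would bias the results.

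**The concern.** The rule suits scales filled in once per visit under supervision. The app and actigraph data differ in two ways. Each wave yields many values per patient, and those values are produced at home, where prompts can be missed and nights lost. The number of observations will therefore vary between patients and waves.

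A completer MANOVA handles this badly. It needs a full set of repeated values for each patient, so a patient with two good waves and one missing wave contributes nothing to a three-wave analysis. If each wave is reduced to one summary, a summary of a handful of prompts counts as much as a summary of 54. Emotional regulation and sleep are secondary goals and part of the first hypothesis, so selection towards compliant patients would affect results the authors intend to report.

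**Working it through.** **Inputs.** 6 prompts a day, 9 days, 3 waves (Ecological momentary assessments; section on T1–T3). 44 patients per group, 88 in total (Recruitment). The article gives no response or dropout rates, so every rate below is an assumption.

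**The plan's own figure.** For a two-sample t-test with d = 0.7 and two-sided alpha 0.05, the exact noncentral-t power is 0.894 with 43 per group and 0.901 with 44. The stated 88 is reproduced. With two groups, error df = 88 − 2 = 86.

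**Can the test be computed?** The multivariate test needs at least as many error df as within-patient contrasts (number of repeated values minus 1).

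| Repeated values, one item or measure | Values | Contrasts | Against 86 error df |
|---|---|---|---|
| Prompts, one wave | 6 × 9 = 54 | 53 | computable |
| Prompts, two waves | 108 | 107 | not computable |
| Prompts, three waves | 162 | 161 | not computable |
| Actigraph nights, three waves | 9 × 3 = 27 | 26 | computable |
| One summary per wave | 3 | 2 | computable |

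Three app items analysed jointly as wave summaries give 2 × 3 = 6 contrasts, also computable.

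**Who stays if every prompt were required?** Expected completers are 88 × c^54 for one wave and 88 × c^162 for three, with c the chance that a prompt is answered, independently.
- c = 0.95: 5.5 and 0.02 patients.
- c = 0.99: 51 and 17 patients.

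Clustering of responses within patients raises these counts: beta-distributed rates with mean 90% left about 5 to 14 of 88 for all 162 prompts. For nights, 88 × 0.95^27 = 22 and 88 × 0.99^27 = 67.

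**Who stays if one summary per wave is required?** Let w be the share of patients who supply a usable wave, independently across waves. Expected completers are 88 × w² for T1–T2 and 88 × w³ for T1–T3.
- w = 0.95: 79 and 75.
- w = 0.90: 71 and 64.
- w = 0.80: 56 and 45.

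What counts as usable matters. If at least 27 of 54 prompts were required at all three waves, the expected number is 88 × [P(Bin(54, c) ≥ 27)]³: about 15 at c = 0.50, 75 at 0.60 and 88 at 0.70. With at least 18 of 54 it is about 87 at c = 0.50. Dropout between waves is not counted in these threshold figures.

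**Unequal precision.** If prompts within a wave were independent, the within-wave part of the variance of a mean is proportional to 1/n. A mean of 5 prompts then carries 54/5 = 10.8 times that part of the variance of a mean of 54. MANOVA on wave means ignores the difference. Correlated prompts would reduce the ratio.

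**The case against.** The strongest reply is that the plan never prescribes a prompt-level MANOVA. Throughout the article, measurement or assessment times are T1 to T4, the whole app period lies within one measurement point, and the Discussion places at least 3 months between assessments. A missed prompt therefore removes nobody. Reduction to a summary is also normal in this article: attentional-task response times become bias indexes before analysis. How prompts are scored, and how many are needed, is commonly left to a full protocol or analysis plan. Finally, sleep and emotion regulation are also measured by supervised questionnaires, the ISI and the CERQ.

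Most of this stands. A reader might infer that the daily-emotion analysis cannot be run, or would keep almost no patients. The documents do not support that, because both depend on treating each prompt as an assessment time. A reader might also extend the degrees-of-freedom problem to the actigraph, but 26 contrasts against 86 are estimable, and wearing the device asks little beyond recharging it. The lack of a scoring rule is not an error in a journal article.

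The reply does not remove the rule that is written. Completer MANOVA is fixed for each variable without exception. Even on the favourable reading it discards patients with a missing needed wave and ignores how much data lies behind each summary. The supervised-completion argument does not reach data collected at home.

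**Conclusion.** The point holds as a choice of a weaker method for secondary outcomes and should be changed. On the natural reading the planned MANOVA is feasible. Its cost is the loss of patients with partial data (about 24 of 88 over three waves, or 17 of 88 for T1–T2, if 90% supply each wave) and equal weight for sparse and full waves. The true loss is unknown, because the article gives no response or dropout rates, and it could be small if compliance is high. The non-computable case (161 or 107 contrasts against 86) applies only to a prompt-level analysis across waves, which the article does not say it intends.

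The fatigue outcome, the sample size of 88, and the ISI and CERQ analyses are not affected by this point.

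**What to change.** In Statistical analyses, exempt the app and actigraph outcomes from the completer-MANOVA rule. Analyse all answered prompts with a linear mixed model: fixed effects for arm, wave and arm-by-wave, and random effects for participant, wave within participant and day within wave. For nightly or daily actigraph values, use random effects for participant and wave within participant. Report the T1–T2 arm-by-wave term, with its confidence interval, as the result. T1–T2 is the safer controlled contrast, because the waiting-list group receives the intervention at the latest 4 months later.

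The change costs a sentence or two and uses standard software, with no new data. The downside is the assumption that unanswered prompts and lost nights are missing at random given the observed data. It would fail if, for example, patients skip prompts when they feel worst in ways their other answers do not show. A completer analysis generally needs a stronger assumption.

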### Data coding and storage

Most questionnaires are completed electronically (on a computer) by the participants. Data encoding will be assured by an independent team, in an automatic computerized way. They have no contact with the patients. Final databases, and manually coded data (data from the actigraphs, partners’ questionnaires) are stored on the experimenter’s computer, protected by a password.

### Statistical analyses

Baseline (T1) demographic, medical, and psychological data will be compared between groups to test for initial groups equivalency using inferential statistics, including analyses of variance (ANOVA) and chi-square tests. Group-by time changes, and pre- and post-assessment comparison of each variable within each group will be assessed using repeated measures MANOVA, on the participant who completed all the needed assessments times. The link between a decrease in distress and attentional bias will be assessed by correlations. Correlations will also be used to assess the links between the data from the patients and their partners, and we will measure the evolution of the partners using repeated measures MANOVA. All tests will be two-tailed, and the alpha will be set at 0.05. Statistical analyses will be performed after T3 and after T4.

All participants will be informed by e-mail about the final results of the study. Scientific publications will also be planned.

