## Methods and design

### Design

Figure 1 illustrates the longitudinal randomized waiting-list controlled trial design used in our study. Ethics approval has been obtained from the Comité d’Ethique Hospitalo-Facultaire Universitaire de Liège. The waiting-list control design allows every participant to benefit from the intervention, which will make it possible to recruit more patients than in a no-treatment control design. It also controls the influence of natural recovery from cancer treatments and spontaneous improvement or deterioration of symptoms [59]. Each intervention will start when 16 patients have successfully completed the screening and the first measurement time (T1). Those patients will be randomized into two groups of eight participants: the first group will receive immediate intervention (intervention group) and; the second group will receive it (at the latest) 4 months later (waiting-list control group).

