**Fig. 1 Fig1:**
[figure not shown]
Design of the study

The randomization process will be conducted by the principal investigator. Our clinical experience showed us that breast cancer patients are more likely to participate in such intervention. Despite the fact that we do not aim to compare the efficacy of our intervention between different cancer diagnoses, we will ensure that cancer diagnoses are equally allocated between the two groups (experimental vs control) because we want the same number of breast cancer patients in each of these groups. The researcher will conduct two randomizations: one for the breast cancer patients, and one for the other cancer patients. The draw will be operated through a specialized website (https://www.dcode.fr/tirage-au-sort-nombre-aleatoire) in which the investigator will introduce the codes of the participants and ask the software to divide them into two groups (experimental and control groups). The participants do not know the group in which they are included (experimental vs control) until the end of the first evaluation, when the experimenter tells them (T1). The first intervention group started in April 2017, and the waiting-list control group started in July 2017.

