### Recruitment

Participants will be recruited over a 2-year period at the University Hospital of Liège (Belgium). Potentially eligible participants are identified in several ways. First, healthcare professionals working with cancer patients (mostly oncologists, radiotherapists, psychologists, and nurses) are informed of the study and asked to talk about it to their non-metastatic patients who have finished their treatment. Interested patients should directly report to the experimenter or are advised to contact us by phone. Second, flyers and posters are displayed in different strategic areas in the hospital (mostly in oncology, radiotherapy, and algology services’ waiting rooms), which allow other health professionals and patients to be informed about the study and to contact us to participate or to talk about the study. Finally, in collaboration with the social nurse, all eligible patients are directly met after their last radiotherapy session, and are offered to participate in the study. Review of the trial process and difficulties encountered are discussed once a month between the researchers. This permitted to improve our recruitment strategies.

The recruitment started in December 2016 and is ongoing. Sample size has been determined by a power analysis in order to detect a difference in the evolution of data between the two groups. The sample size calculation was based on an independent samples t-test for a difference in mean scores. Alpha was set at 0.05, power at 90% and the standardized effect size at 0.7. The Cohen’s *d* of 0.7 is considered to be a medium to high effect size. Psycho-oncology studies which aim to assess the effect of an intervention on the patients’ quality of life often use effect sizes between 0.6 and 0.8 to calculate the sample size [62, 63]. According to this analysis, 44 patients are required in each group for a total of 88 patients.

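### Baseline significance tests and a change-based efficacy test give up precision that adjusting for the T1 score would provide at no cost

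*Protocol article*

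**What the plan says.** Under Statistical analyses, baseline demographic, medical and psychological data "will be compared between groups to test for initial groups equivalency using inferential statistics", by ANOVA and chi-square. Efficacy is then assessed as group-by-time change, together with within-group pre/post comparisons, by repeated measures MANOVA in participants with all the needed assessments. In that model T1 is one of the repeated outcomes; no covariate is named. On error rates: "All tests will be two-tailed, and the alpha will be set at 0.05".

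Under Design, allocation is 1:1 in sets of 16 ("Those patients will be randomized into two groups of eight participants") and T1 is complete before each intervention starts. Allocation is stratified: "The researcher will conduct two randomizations: one for the breast cancer patients, and one for the other cancer patients".

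Under Recruitment, the trial is sized "in order to detect a difference in the evolution of data between the two groups", yet "The sample size calculation was based on an independent samples t-test for a difference in mean scores". The inputs are "Alpha was set at 0.05, power at 90% and the standardized effect size at 0.7", and the result is that "44 patients are required in each group for a total of 88 patients".

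**The concern.** Two choices that the article itself makes are at issue.

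First, if allocation is sound, any T1 difference between arms arose by chance. A test of baseline equivalence therefore asks a question whose answer is already known, and a non-significant result does not show equivalence. The article gives no consequence for a significant one. With many scales some will be significant: Table 1 names 17 patient scales at T1 besides the visual analogue scales, so one 5% test each gives 17 × 0.05 = 0.85 expected false positives. That invites covariate choices made after seeing the data.

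Second, over two waves the group-by-time test is the same as a t-test on change. Change subtracts the whole T1 score, whereas ANCOVA subtracts only the part that predicts T2. Under randomisation both estimate the same effect without bias, and ANCOVA is the more precise for every r below 1. What is at stake is the width of the confidence interval for fatigue and for every other T2 outcome.

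**Working it through.** **Inputs from the article.** d = 0.7, alpha 0.05 two-sided, power 90%, independent-samples t-test, 1:1 allocation, 44 per arm.

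**Assumed.** The T1–T2 correlation r is not given; I use 0.3 to 0.8, with equal SDs at T1 and T2.

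**Step 1: the plan's own figure.** The noncentrality is 0.7 × √(44/2) = 3.28 on 86 df. Exact noncentral-t power is 90.1%, and 44 is the smallest group size reaching 90%. The stated 88 is reproduced.

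**Step 2: variances, relative to an unadjusted T2 score.**
- Change: 2(1 − r)
- ANCOVA on T1: 1 − r²
- Ratio of ANCOVA to change: (1 − r²) / [2(1 − r)] = (1 + r)/2

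The ratio is 0.65 at r = 0.3, 0.75 at 0.5 and 0.90 at 0.8, which are reductions of 35%, 25% and 10%.

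**Step 3: power at 44 per arm if d = 0.7 is in raw-score SD units.** The effective d is 0.7/√[2(1 − r)] for change and 0.7/√(1 − r²) for ANCOVA, which loses one further df. At r = 0.5 these are 0.700 and 0.808.

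| r | Change | ANCOVA | n per arm for 90%: change / ANCOVA |
|---|---|---|---|
| 0.3 | 78.3% | 92.5% | 62 / 41 |
| 0.4 | 84.2% | 94.3% | 53 / 38 |
| 0.5 | 90.1% | 96.3% | 44 / 34 |
| 0.6 | 95.2% | 98.2% | 36 / 29 |
| 0.7 | 98.7% | 99.5% | 27 / 23 |
| 0.8 | 99.9% | >99.9% | 19 / 17 |

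**Step 4: power if d = 0.7 is in change-score SD units.** Change has 90.1% whatever r is. ANCOVA has effective d = 0.7/√[(1 + r)/2], giving 98.1% at r = 0.3, 96.3% at 0.5 and 92.8% at 0.8.

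**Step 5: if the MANOVA takes in T1, T2 and T3.** The interaction then has 2 df. With equal correlations of 0.5 and 44 per arm, power is 92.6% if the 0.7 effect holds at both follow-ups and 83.1% if it halves by T3. Single-time ANCOVA at T2 has 96.3%.

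**Step 6: the stratum term.** If breast and other patients differ by an assumed 0.2 to 0.5 SD, and breast patients are 50% or 70% of the sample, removing that variance lifts the 90.1% to 90.3–91.7%. A simulation used 52 breast and 36 other patients, r = 0.5, and a 0.5 SD difference appearing at follow-up only. Without the stratum, type I error was 0.045 (change) and 0.041 (ANCOVA); with it, about 0.05. Power rose from 88.7% to 89.8% for change and from 95.3% to 96.0% for ANCOVA.

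**The case against.** The strongest reply is that the planned test is valid and may already have its 90% power. That stands. A reader might infer from the 78% and 84% figures that the trial is underpowered, or that it was sized for a different test. The article does not support this. It says both "The sample size calculation was based on an independent samples t-test for a difference in mean scores" and that the aim was "in order to detect a difference in the evolution of data between the two groups". If d is in change-score units, the planned test has 90.1% at any r. Even in raw-score units a shortfall needs r below 0.5, and nothing in the article supports or excludes that.

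Three further objections also stand:
- The table describes a two-wave test. A three-wave MANOVA has different power (Step 5).
- Eligibility does not require fatigue, and a reader might think the resulting spread in T1 fatigue makes ANCOVA especially worthwhile. Against the planned change test it does not: more between-patient spread tends to raise r, and (1 + r)/2 then moves towards 1.
- It is tempting to say that omitting the stratum misstates the standard error or wastes the stratification. In the simulation the test was only slightly conservative. The stated reason for stratifying was equal numbers of breast cancer patients per arm, which the allocation delivers by itself.

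Finally, an article condenses a fuller plan, and covariates may be listed elsewhere. This weakens the stratum part most. It does not remove the core, because the equivalence tests and the group-by-time analysis are stated in the article itself.

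**Conclusion.** The point holds as a free improvement, not as an error. The baseline tests serve no purpose, although nothing in the article makes the conclusions depend on them. For a T1–T2 comparison, ANCOVA cuts the variance by 35% to 10% over the assumed r of 0.3 to 0.8. The power gain at 44 per arm depends on two things the article does not settle: r and the SD units of d. In raw-score units it is about 14 points at r = 0.3, 6 at r = 0.5 and almost nothing at r = 0.8. In change-score units it is about 8 down to 3 points over the same range. Nearly all of this comes from the T1 score; the stratum adds about 0 to 2 points. No bias is claimed, and the sample size is not wrong for its own inputs.

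**What to change.** Replace the baseline ANOVA and chi-square tests with a descriptive baseline table by arm, without p-values. Estimate the between-arm difference at T2 by ANCOVA, with the T1 value of the same outcome and the breast/other stratum as prespecified covariates, and report it with a confidence interval. Use the same form for each outcome measured at both T1 and T2. The stratum term is there mainly to match the analysis to the randomisation and keep the test at its nominal level. A term for the randomisation set of 16 is optional; its gain has not been quantified. It would also help to state whether d = 0.7 refers to raw or change scores.

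The cost is a revised analysis paragraph and a different, standard model. T1 scores and diagnosis are already collected before the intervention starts, and the sample size need not change.

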There are some limitations of our study. The number and length of assessments completed by the participants could lead to some dropouts. It is possible that only motivated and compliant patients will complete all the assessments, which would bias the results of the study. However, it is important to point out that the participants have to complete assessments with at least a 3-month interval between them, which reduces the possible burden experienced by the participants. Another limitation is the fact that our intervention has only been proposed for non-metastatic patients in order to minimize the baseline differences of the sample.

In conclusion, our study will provide the initial insight into the short and long-term effects of an intervention combining hypnosis and self-care on the quality of life of all types of cancer patients in remission, on partners’ well-being, on the quality of the conjugal relationship, and on links between emotional regulation, distress, and attentional bias.

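### The efficacy analysis is restricted to patients who complete all needed assessments, although the protocol acknowledges that selective completion is possible and would bias the results

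*Protocol article*

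**What the plan says.** All references are to the protocol article.

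- **Analysis population.** Statistical analyses assigns both the group-by-time comparison and the within-group pre/post comparison to "repeated measures MANOVA, on the participant who completed all the needed assessments times". The article describes no analysis of all randomised patients. Analyses are to be run after T3 and again after T4.
- **Dropout.** The limitations paragraph of the Discussion says "The number and length of assessments completed by the participants could lead to some dropouts", and then "It is possible that only motivated and compliant patients will complete all the assessments, which would bias the results of the study". The only mitigation offered is that assessments are at least three months apart.
- **Missing responses.** One-year follow-up (T4) calls missing responses very unlikely, because the investigator checks each questionnaire. It also expects good attendance at the one-year session, without a rate. The Intervention section says that reasons for dropping out are recorded, but gives them no role in the analysis.
- **Blinding and burden.** Under Measurement points, patients learn their allocation at the end of T1. Each measurement point has two sessions, of about 2 h 30 min and 1 h 15 min, with nine days of monitoring between them.

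**The concern.** Repeated-measures MANOVA in this form is listwise deletion: a randomised patient who misses a needed time contributes nothing to that analysis. Randomisation makes the two arms comparable at entry. It does not make the completers of one arm comparable with the completers of the other.

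Differential loss is plausible here. Patients know their arm from the end of T1. One arm starts eight weekly sessions with home tasks, while the other waits up to four months. Reasons for leaving need not be the same in the two arms.

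The primary goal, an effect on fatigue, rests on this comparison. Where T3 is one of the needed times, the rule also discards T2 data already collected from patients who later miss T3. The article states this rule outright, so it is not a detail left to another document: an analysis plan that used all randomised patients would contradict the sentence.

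**Working it through.** **1. Does the sample size allow for loss?** Inputs from Recruitment: the calculation uses a t-test comparing two independent means, with these settings: "Alpha was set at 0.05, power at 90% and the standardized effect size at 0.7". The result given there is that "44 patients are required in each group for a total of 88 patients". Allocation is 1:1 (Design: "Those patients will be randomized into two groups of eight participants"), and Statistical analyses confirms two-sided testing.

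- Normal approximation: n per arm = 2(1.960 + 1.282)² / 0.7² = 42.9, so 43.
- Exact t-test: with 44 per arm, noncentrality = 0.7 × √(44/2) = 3.28 on 86 degrees of freedom, power 90.1%. With 43 per arm, power is 89.4%.

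The stated 44 per group reproduces exactly and contains no dropout allowance.

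**2. How large could the bias be, and in which direction?** All of the following are assumptions, as the documents give no rate or mechanism. Scores at T1 and T2 are standard normal with higher meaning worse, correlation ρ = 0.5, and no true effect. The waiting arm is complete, so its mean change is 0. In the intervention arm, logit P(dropout) = a + x, with a = −1.65 to give 20% loss. Here x is the score that drives dropout.

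The mean of x among those who stay is δ = E[x(1 − p(x))] / 0.80 = −0.173 (numerical integration). The other score shifts by ρδ = 0.5 × (−0.173) ≈ −0.087.

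| Dropout follows | Stayers' T1 mean | Stayers' T2 mean | Completer contrast in change |
|---|---|---|---|
| worse T2 score | −0.087 | −0.173 | about −0.09 SD (favours intervention) |
| worse baseline score | −0.173 | −0.087 | about +0.09 SD (against intervention) |

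The size is (1 − ρ)|δ| in both rows; only the sign changes.

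**3. What range is possible?** For a comparison of means at one time, with loss rate r in one arm only and correlation c between the propensity to leave and a worse outcome, the completer mean shifts by c·φ(z_r)/(1 − r).

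- r = 10%, c = 0.3: 0.3 × 0.175 / 0.9 = 0.06 SD
- r = 20%, c = 0.5: 0.5 × 0.280 / 0.8 = 0.175 SD
- r = 30%, c = 0.5: 0.5 × 0.348 / 0.7 = 0.25 SD

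The rejection rate of a nominal 5% test with no true effect rises to about 6%, 12% and 18% respectively. If both arms lose patients equally and equally selectively, the shifts largely cancel.

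**4. Does a mixed model remove the bias in step 2?**

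- *Dropout follows baseline, which is observed.* The stayers' regression of T2 on T1 has slope 0.50, so the estimated T2 mean is −0.087 + 0.50 × 0.173 = 0. The bias is removed.
- *Dropout after T2 follows the observed T2 score, and T3 is missed.* The completer rule still shifts the T2 contrast by about 0.09 SD. Using all available data, the bias is 0 at T2 and at T3.
- *Dropout follows a T2 score that is never observed.* The stayers' slope is 0.457, giving −0.173 + 0.457 × 0.087 ≈ −0.13 SD. The bias is not removed, and is larger than the 0.09 SD of the completer change contrast.

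**The case against.** The strongest defence is that loss may be small. Questionnaires are checked on the spot, and good attendance is expected at the one-year session. The first point prevents missing items at attended visits, not missed visits or withdrawal. The second concerns T4 only and carries no figure. Neither repairs the rule.

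Several stronger readings are tempting, and the documents do not support them:

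- *That the authors expect selective dropout.* They say that dropout could occur and that selective completion is possible.
- *That every randomised patient with any missed visit is excluded throughout.* The text refers to the needed times, which may be T1–T2, T1–T3 or T1–T4 depending on the analysis. The loss of T2 data is therefore conditional on T3 being needed.
- *That the bias must favour the intervention.* Step 2 of the working shows that the sign depends on the mechanism, about which the documents are silent.
- *That listwise deletion costs the trial its power.* With 39, 35 or 30 completers per arm (10%, 20% or 30% loss), power at d = 0.7 is 86.3%, 82.3% or 76.0%. Those falls come from a sample size with no dropout allowance. A mixed model would not generally restore them, because patients with only T1 add little information on the group difference.
- *That losses by T4 damage the randomised contrast.* T4 falls one year after each patient's own course, when both arms have been treated.

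It is also fair to object that a mixed model is no cure when leaving depends on an outcome nobody saw. That objection stands, and it shapes the fix.

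**Conclusion.** The point holds. The article fixes a completers-only population for its efficacy tests and itself names the bias that this could bring; nothing elsewhere in it offsets the rule. The randomised comparison is not necessarily lost, but it is no longer protected.

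The size cannot be read from the documents. Under the stated illustration (20% loss in one arm, log-odds 1 per SD, T1–T2 correlation 0.5, zero true effect) it is about 0.09 SD in either direction, roughly one eighth of the planned 0.7 (0.087 / 0.7 = 0.12). With equal and equally selective loss it would be near zero. The case for change rests on the principle, the authors' own concession and the low cost of repair, rather than on a demonstrated magnitude.

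**What to change.** In Statistical analyses, replace the completers-only MANOVA as the efficacy analysis with the following:

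1. Analyse all randomised patients in their allocated group, using a likelihood-based linear mixed model for repeated measures on all available T1–T3 data. Include group × time and an unstructured covariance, with baseline either constrained equal across arms or adjusted for.
2. Make a missing-not-at-random sensitivity analysis, with worse outcomes assumed for those who drop out, a required part of the plan. The mixed model handles dropout that depends on observed baseline or T2 scores, but not dropout that depends on unobserved ones.
3. Keep the completer analysis as supportive, and state which times are needed for it.

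Separately, state that 44 per group contains no dropout allowance. Keeping 44 completers per arm would need 44/0.9 = 49, 44/0.8 = 55 or 44/0.7 = 63 randomised per arm at an assumed 10%, 20% or 30% loss. Recruiting more patients would restore power but would not remove bias.

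Changing the analysis costs a wording change and modest extra work, with no new data. The resulting estimates may be less favourable to the intervention.
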